### Secondary outcomes

The HRV will be calculated from the series of RR intervals captured by the cardiofrequency monitor using linear methods. It will be analyzed in the time and frequency domains. A Poincaré plot will be used. All HRV indices will be calculated by Kubios HRV software version 3.1.0.

The RR interval series was recorded before and after the 12 weeks of training. There were 1000 RR intervals in each data set. In addition, daily tracking of each session will be analyzed. Stretches of 256 consecutive RR intervals were recorded every 5 minutes. In both analyses, the most stable stretches were used to avoid any bias in the analysis and data interpretation [5]. The time series of RR intervals will undergo moderate digital filtering using Kubios, supplemented by manual filtering to eliminate premature ectopic beats and artifacts. Only series with more than 95% of sinus beats will be included in the final analysis [23].

The time domain (rMSSD and standard deviation of all RR intervals) [24], frequency (low and high) [23, 25, 26], and Poincaré plot (standard deviation of data from *x* = *y* and standard deviation of data from the line orthogonal to *x* = *y* that passes through the mean value of the data) [23, 27, 28] HRV indices will be used for the analyses before and after the 12 weeks of training. Only the time domain indices and the Poincaré plot will be used for daily tracking.

HR [23], respiratory rate measurements [29], and oxygen saturation [30] were captured. Blood pressure [31] was measured. A subjective pain assessment was obtained through a visual analog pain scale [32, 33]. Volunteers were asked to fill out a psychometric questionnaire [17] before and after the training period, as well as before all training sessions.

All these outcomes were collected in the initial evaluation and in the final evaluation after the 12 weeks of training, in addition to before and after each Pilates session. Table 1 lists outcome collection time points.

**Table 1 Tab1:** Time points for outcomes

Outcomes			Time point				
			Initial assessment	Final evaluation	During the sessions		
					Before and at the end	Every 5 min	15 min after
Primary	Load monitoring	Borg			X	X	X
		HR			X	X	X
		rMSSDmean			X	X	
		rMSSDcv			X	X	
Secondary	ANS	HRV	X	X	X	X	
	Cardiorespiratory metrics	BP	X	X	X		
		HR	X	X	X		
		*f*	X	X	X		
		SatO_2_	X	X	X		
	Pain	VAS	X	X	X		
	SPE	Borg	X	X			

*SPE* subjective perception of effort, *HR* heart rate, *ANS* autonomic nervous system, *HRV* heart rate variability, *BP* blood pressure, *VAS* visual analog scale, *f* respiratory rate, *SatO*_*2*_ oxygen saturation, *rMSSD* parasympathetic modulation index, *rMSSDmean* weekly mean of rMSSD expressed in milliseconds, *rMSSDcv* weekly intra-individual coefficient of variation of rMSSD

### Masking and blinding

Baseline outcomes were collected prior to randomization. The final evaluation was conducted by trained evaluators blinded to group allocation. In addition, data were collected throughout the Pilates training period by independent evaluators. The study statistician will also be blinded. In this study, it was not possible to blind either the participants or the therapist who administered the Pilates sessions.

### Sample size calculation

The sample calculation was carried out based on Barbosa et al*.* [34] with the rMSSD index. The clinically relevant difference was 19,02 ms and the standard deviation 23,94 ms. For a two-tailed hypothesis test, the significance level for the sample calculation was 5% and the power of the test was 80%. The sample size was calculated to be 25 per group. To account for withdrawals, the sample size was increased by 10% to give 27 volunteers per group.

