**Methods/design:**

In total, 54 healthy men underwent 36 sessions of Pilates mat work. Before each training session, cardiorespiratory measures, pain (visual analogue scale), and a psychometric questionnaire were collected. Heart rate (HR), subjective perception of effort (SPE), and RR intervals were measured during the sessions and used later in the analysis of the progression of training load by monitoring the internal training load and heart rate variability. At the end of the sessions, cardiorespiratory measures, the visual analogue scale, and the psychometric questionnaire were measured again. After 15 min of rest, the final HR measurement was made and the participants noted the effort on the SPE scale. The psychometric, cardiorespiratory, and autonomic measures were evaluated before and after each of the 36 training sessions.

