**Fig. 2 Fig2:**
[figure not shown]
Study outline. VAS visual analog scale BP blood pressure, HR heart rate, *f* respiratory rate, SatO_2_ oxygen saturation, SPE subjective perception of effort

At the end of the 36 Pilates training sessions, the final evaluation was carried out. This included cardiorespiratory measures, the psychometric questionnaire, and HRV. The control group underwent only the initial and final evaluations, like the Pilates group.

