### Primary outcome

Quantification of the internal training load was evaluated in each training session with the three monitoring tools: SPE [6], HR [18], and HRV [18]. For the monitoring to be considered successful, two of the three monitoring tools must yield significant results. In addition, the correlation between SPE and HR should be moderate to high so that they can be used in clinical practice as low cost and easily applicable tools.

The SPE consists of a scale proposed by Borg where the participants choose the descriptor and number that best represents their psychophysiological stress in the training session [6]. It is a scale from 6 to 20 points, where 6 means “no effort” and 20 means “maximum effort.” To avoid biased responses, the question was standardized as: “From 6 to 20 points, how do you rate your perception of effort now?” All responses were recorded in individual records. The participants had previously been made familiar with the scale [6].

Prior to the sessions, participants were told how to estimate their SPE. It was explained to them that during the exercises it was necessary to perceive how much effort they were using so that every 5 minutes during a session they could estimate the SPE according to their individual perception for how exhausting the exercises were.

In addition, 15 min after the end of each session, the participants estimated the SPE again [6]. This final SPE was multiplied by the duration of the session in minutes, and the product represents the internal load in arbitrary units. The intensity of the session was classified into three zones according to the Borg scale used by Moreira et al. [19].

Quantification of the internal load training using the HR was performed using the TRIMP method. This evaluates the volume and intensity of the session through specific scores in each training zone, as proposed by Edwards [18, 20].

In addition to these methods for monitoring the training load, HRV was analyzed. The weekly mean of rMSSD (rMSSDmean) expressed in milliseconds and the weekly intra-individual coefficient of variation of rMSSD (rMSSDcv) expressed as a percentage will be used [21, 22]. These indices will be transformed to logarithms to mitigate outliers and simplify the analysis.

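### The 80% power belongs to a two-group rMSSD comparison listed as secondary; the primary load outcome exists only in the Pilates arm and the sample size was not calculated for it

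*Protocol article*

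**What the plan says.** All references are to the protocol article.

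- **Sample size calculation.** The trial is sized "with the rMSSD index": "The clinically relevant difference was 19,02 ms and the standard deviation 23,94 ms". With a two-tailed 5% test and 80% power this gives 25 per group. For withdrawals, "the sample size was increased by 10% to give 27 volunteers per group".
- **Primary outcome.** "Quantification of the internal training load was evaluated in each training session with the three monitoring tools": perceived effort (SPE), heart rate and HRV. The HRV tool is the log-transformed weekly mean and weekly coefficient of variation of rMSSD. Success needs significant results on two of the three tools. The SPE–heart rate correlation should also be at least moderate.
- **Table 1.** The rows for the primary load measures are marked only in the columns for time points during the sessions. HRV at the initial and final assessments is in the secondary block.
- **Study outline, text after Fig. 2.** "The control group underwent only the initial and final evaluations, like the Pilates group".
- **Study design.** Only the Pilates group trains. Controls are asked to do no exercise training.
- **Abstract, Methods/design.** "In total, 54 healthy men underwent 36 sessions of Pilates mat work".
- **Statistical analysis.** Weekly load differences are assessed by magnitude-based inference. Between-group comparisons use an unpaired t test or a Mann–Whitney test.

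**The concern.** A sample size section normally supports the primary outcome. Here the calculation and the primary outcome concern different quantities in different sets of men. The calculation is a Pilates-versus-control difference in rMSSD in milliseconds. The primary outcome is a within-arm series of session loads with no counterpart in controls.

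The article gives no target effect, within-person variability or target precision for the primary outcome, yet it sets a success rule that depends on significance and on the size of a correlation. A reader could carry the 80% over to that rule. The abstract adds to the risk because it suggests that session data come from 54 men, twice the number planned for the Pilates arm.

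The withdrawal allowance is also slightly short, so even the contrast that was sized falls a little below 80% if the anticipated 10% are lost and not analysed.

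**Working it through.** **Inputs (Sample size calculation).** Difference 19.02 ms; SD 23.94 ms; two-sided alpha 5% (z = 1.960); power 80% (z = 0.8416); 25 per group before and 27 after the allowance. Equal allocation is inferred from 27 per group.

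**1. Reproducing the 25.** The standardised difference is d = 19.02/23.94 = 0.794. For two independent means:

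n per group = 2 × (1.960 + 0.8416)² / d² = 2 × 7.849 / 0.6312 = 24.87, rounded up to 25.

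Alternatives:

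| Calculation | n |
|---|---|
| Two groups, two-sided, normal approximation | 24.87 → **25** |
| Two groups, two-sided, t test | 25.87 → 26 |
| Two groups, one-sided, normal approximation | 20 |
| One group, 23.94 taken as SD of change, normal approximation | 12.43 → 13 |
| One group, 23.94 taken as SD of change, t test | 14.47 → 15 |

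Only the two-group, two-sided calculation gives 25. The t-test version differs from it by one man per group.

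**2. Which outcome can that comparison use?** It needs rMSSD in both groups.

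| | Sized contrast | Primary outcome |
|---|---|---|
| Measure | rMSSD in ms | SPE load, heart-rate load, weekly log rMSSD mean and CV |
| When | Initial and final evaluations, the only ones controls had | Each Pilates session |
| Who | Both groups, 2 × 27 = 54 planned | Pilates group only, 27 planned |
| Method | Unpaired two-group test | Weekly magnitude-based inference, correlations |
| Rank | Secondary | Primary |

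The two columns differ in every row. rMSSD appears in both, but not as the same variable.

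**3. The abstract.** The 54 equals 2 × 27, and Trial status gives it as the number randomized. Study design and Study outline confine the 36 sessions to one of the two groups. Both statements cannot be right.

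**4. The withdrawal allowance.** To keep 25 after 10% loss: 25/0.90 = 27.8, so 28 per arm. Simple inflation, 25 × 1.10 = 27.5, also rounds up to 28. With 27 per arm, 27 × 0.90 = 24.3, so about 24 remain.

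Power for the rMSSD contrast is Φ(d√(n/2) − 1.960) by the normal approximation, and comes from the noncentral t distribution for the t test:

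| n per arm | Normal approximation | t test |
|---|---|---|
| 24 | 78.6% | 76.9% |
| 25 | 80.2% | 78.6% |
| 27 | 83.1% | 81.7% |

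Like for like, going from 25 to 24 costs 80.2 − 78.6 = 1.6 points or 78.6 − 76.9 = 1.7 points.

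**The case against.** **rMSSD is one of the primary tools, so the calculation does relate to the primary outcome.** This is true of the name only. The primary version is weekly, logged and recorded in Pilates sessions. No two-group difference in it can be formed.

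**The article never says that the 80% applies to the primary outcome.** This stands. The sample size section names rMSSD and stops there. The fault is that it does not say which analysis it supports, and nothing else in the article supports the primary one.

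**The withdrawal shortfall is trivial.** This largely stands. It is one man per arm. Statistical analysis keeps everyone assessed at the start, with the worst outcome imputed, and Trial status reports all participants as attending. If all 27 per arm are analysed, power by t test is 81.7%. That figure is not assured either: imputation alters both the difference and the SD, and the Participants section excludes men for injury, low attendance, failure to progress or RR-interval errors.

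**Stronger readings the documents do not support.**
- *Power is 77%, not 80%.* Comparing 76.9% with 80% mixes the loss of one man per arm with a change of formula. Using the normal approximation for 25 is not an error in the plan.
- *The primary analysis is underpowered.* No target effect is stated, so this cannot be shown. A correlation interval that treats each man as one value would not match the planned data, which are taken every 5 minutes over 36 sessions.
- *The unranked secondary tests carry a large, calculable false-positive risk.* Such a figure needs independent tests, whereas several HRV indices come from the same recording. Ranking secondary outcomes is also commonly left to an analysis plan that is not shown.

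**Conclusion.** The point holds. The stated 80% power describes a between-group rMSSD contrast that the article lists as secondary. The primary outcome is a single-arm analysis of about 27 planned men, for which the article gives no sample size basis. The abstract's count of trained men is contradicted by the article itself. The withdrawal arithmetic is a minor addition: 28 rather than 27 per arm, worth 1.6 to 1.7 power points against 25.

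The conclusion rests on three things. The first is reading the calculation as a two-group test, which its own numbers support. The second is taking 27 as the Pilates arm; this is the planned figure, since the text does not give the actual split of the 54. The third is that the article does not say whether 19.02 ms is a difference in final values or in change. That question does not affect the mismatch, but only the authors can settle it.

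A reader might infer that before/after rMSSD should now become the confirmatory outcome. The documents do not support that step: Trial status says that data were collected in June 2019, and reordering outcomes after collection would create a problem of its own.

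**What to change.** 1. In Sample size calculation, state that the figure covers the between-group rMSSD contrast, have the authors specify final values or change, and say that it is not the basis for the primary load analysis.
2. State that the primary load analysis is single-arm. Report it with confidence intervals that allow for repeated sessions within each man, rather than with a power figure.
3. State that power for the rMSSD contrast is slightly below 80% if 10% are lost and not analysed (78.6% by normal approximation or 76.9% by t test at 24 per arm).
4. Correct the abstract to say that 54 men were randomized and that only the Pilates group did the 36 sessions.

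Items 1, 3 and 4 are wording changes; item 2 also fixes how the primary estimates are reported. None of them needs extra recruitment or a change to the outcome hierarchy. The cost is that the stated power looks slightly less favourable and the primary result can no longer be presented as powered.

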### Statistical analysis

Descriptive statistics will be used, and the results presented as means, errors, standard deviations, percentages, and absolute numbers. The normality of the data will be evaluated through a Shapiro–Wilk test. In the comparison of the population profile and the cardiorespiratory, autonomic, and psychometric measures in the initial and final evaluations, the paired *t* test will be used for normal data or the Wilcoxon test for non-normal data. In the comparison between the groups, the unpaired *t* test or Mann–Whitney test will be used depending on the normality of the data, with the significance level set at *p* < 0.05. Differences based on magnitudes (Δ = final value – initial value) will also be calculated [35, 36] to verify the differences between the initial and final time points.

To analyze weekly differences in training loads using the SPE, HR, and HRV indices (ln rMSSDweekly and ln rMSSDcv) over the 12-week study duration, magnitude-based inferences will be calculated [36].

For ln rMSSDweekly, the smallest worthwhile change was set at 3% [37]. For SPE, HR, and ln rMSSDcv, the smallest worthwhile change is defined as 0.2 × between-subject standard deviation. The quantitative chances to find differences in the variables to be tested will be assessed qualitatively as follows: <1% almost certainly not, 1–5% very unlikely, 5–25% unlikely, 25–75% possible, 75–95% likely, 95–99% very likely, and >99% certain. If the chances of having higher and lower results are both >5%, the true difference was assessed as nuclear [35]. The magnitude of the effect size will be qualitatively interpreted using the following thresholds: <0.2 trivial, 0.2–0.6 small, 0.6–1.2 moderate, 1.2–2.0 large, 2.0–4.0 very large, and >4.0 nearly perfect [35].

To determine the correlations (dose–response) between ln rMSSD, HR, and SPE, Pearson’s or Spearman’s correlation will be used according to the normality of the data. The threshold used to evaluate the correlations quantitatively will be based on Hopkins [35] using the following criteria: <0.1 trivial, 0.1–0.3 small, 0.3–0.5 moderate, 0.5–0.7 large, 0.7–0.9 very large, and >0.9 almost perfect.

The cutoff points for load increments with the HRV indices and SPE were obtained from the receiver operating characteristic curve. The sensitivity, specificity, positive predictive value, and negative predictive value for each level of the Pilates method will also be calculated. The area under the curve will be considered significant when values ≥0.65 are obtained [38]. In addition, a comparison will be made between the receiver operating characteristic curves of each HRV index to detect the most representative for determining the internal training load of the Pilates method.

The statistical analysis will be carried out with the *Statistical Package for the Social Sciences*, version 15.0 (SPSS Inc., Chicago, IL) and *MedCalc Software bvba*, version 14.10.2 (Oostende, Belgium). All data will be entered into the software twice. All participants included in the initial assessment will be considered under the intention-to-treat approach in which the worst outcome obtained by the study group will be selected to ensure the power of the data analysis.

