**Discussion:**

This is a parallel randomized clinical trial of standardized Pilates training, with the aim of estimating training loads and measuring the efficacy of Pilates through clinical, cardiorespiratory, and autonomic outcomes. The protocol can easily be reproduced and could be used to support professionals in prescribing the method.

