Therefore, the objective of this protocol is to monitor the daily load progression from the basic and intermediate levels to the advanced level by measuring HR, SPE, and HRV for 12 weeks, as well as to analyze the effect of the method on psychometric, cardiorespiratory, and autonomic measures. It is hypothesized that the protocol proposed by the study can be prescribed clinically, proving that SPE, HR, and HRV are useful tools for monitoring the progression of Pilates training loads. Furthermore, SPE is expected to have a good correlation with HR and clinical relevance, thus giving practitioners two simple low-cost monitoring tools. In addition, it is hypothesized that the psychometric, cardiorespiratory, and cardiac autonomic modulation measures will have improved after 12 weeks of training.

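### No between-arm comparison is named as the lead efficacy test: at least 12 secondary outcomes are each compared at p < 0.05, while the sample size covers rMSSD alone

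*Protocol article*

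**What the plan says.** The Statistical analysis section first sets out tests for "In the comparison of the population profile and the cardiorespiratory, autonomic, and psychometric measures in the initial and final evaluations", using paired methods within a group. For the randomized contrast it continues: "In the comparison between the groups, the unpaired *t* test or Mann–Whitney test will be used depending on the normality of the data, with the" threshold fixed at p < 0.05. It gives no ordering, adjustment or lead comparison.

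The outcomes concerned are described under Secondary outcomes, where the time-domain, frequency-domain and Poincaré "HRV indices will be used for the analyses before and after the 12 weeks of training". Table 1 also labels the initial/final measures secondary.

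The Primary outcome section concerns something else. It quantifies internal training load in each session with three tools and counts the monitoring as successful if two of the three give significant results. The end of the Study outline section says that controls had only the initial and final evaluations.

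Two places state an efficacy purpose. In the Background, "it is hypothesized that the psychometric, cardiorespiratory, and cardiac autonomic modulation measures will have improved after 12 weeks of training". In the Discussion paragraph of the Abstract, the trial is described as one "with the aim of estimating training loads and measuring the efficacy of Pilates through clinical, cardiorespiratory, and autonomic outcomes". The Sample size calculation rests on one variable, rMSSD: a relevant difference of 19.02 ms, SD 23.94 ms, two-sided 5%, 80% power, 25 per group.

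**The concern.** A secondary label normally limits the damage from many tests because a primary arm comparison carries the efficacy claim. Here the primary outcome cannot do so, since no control data exist for it. The benefit of randomization reaches only the secondary set, and within that set all outcomes stand level.

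The plan therefore powers one arm comparison but does not say that this comparison decides anything. If rMSSD showed no difference and, say, respiratory rate gave p = 0.03, the text would not tell a reader whether Pilates had been shown to work. The 5% level assumed in the sample size applies to each test separately, not to a conclusion drawn from whichever outcomes turn out significant.

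**Working it through.** **Inputs.** Per-test level 0.05 (Statistical analysis). Difference 19.02 ms, SD 23.94 ms, two-sided 5%, power 80%, 25 per group (Sample size calculation). HRV indices from Secondary outcomes, cardiorespiratory measures from Study outline, psychometric questionnaire from both. Correlations between outcomes are not given, so they are assumed and varied.

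**1. The plan's own figure.** n per group = 2 × (1.960 + 0.842)² × (23.94/19.02)² = 24.9, so 25. The stated number is reproduced and corresponds to a single two-sided 5% test of rMSSD. A one-sided 5% test would give 20.

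**2. Counting the arm comparisons.**
- HRV: rMSSD, SD of RR intervals, low frequency, high frequency, two Poincaré SDs = 6.
- Cardiorespiratory: systolic pressure, diastolic pressure, HR, respiratory rate, oxygen saturation = 5.
- Psychometric: at least 1.
- Total: 6 + 5 + 1 = 12. Pain VAS and the initial/final Borg entry in Table 1 would make 14, but the Statistical analysis section does not name them among the measures compared.

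**3. Chance of at least one false-positive arm difference, no outcome truly differing.** For independent tests: 1 − 0.95¹² = 0.46. For correlated tests, normal test statistics with one common correlation were simulated, counting any |z| > 1.96:

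| Tests | Correlation 0 | 0.5 | 0.8 |
|---|---|---|---|
| 11 | 0.43 | 0.30 | 0.18 |
| 12 | 0.46 | 0.32 | 0.19 |
| 14 | 0.51 | 0.35 | 0.20 |

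The row for 11 counts rMSSD once together with the Poincaré SD orthogonal to the line x = y, which is almost exactly rMSSD/√2. If only false differences in favour of Pilates count, the 11-test rates are 0.24, 0.15 and 0.09, against 0.025 for one test.

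A single correlation across all outcomes is crude. Letting correlation act mainly within families (HRV 0.3 to 0.9, cardiorespiratory 0 to 0.5, between families 0 to 0.1, with the rMSSD duplicate) gives about 0.30 to 0.42 for 12 outcomes.

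**4. What flat adjustment would cost.** Bonferroni over 12 tests means 0.05/12 = 0.0042 per test. With 25 per group the standard error is 23.94 × √(2/25) = 6.77 ms, and 19.02/6.77 = 2.81. Power by the normal formula is Φ(2.81 − 1.96) = 0.80 at the 5% level and Φ(2.81 − 2.87) = 0.48 after Bonferroni. The t-based values are 0.79 and 0.43. Restoring 80% would need 44 per group by the normal formula. One lead test at 5% leaves the 25 per group unchanged.

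**The case against.** Several stronger readings are tempting, and the article does not support them.

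- **That the plan has no hierarchy at all.** It has one. A primary outcome is defined with its own success rule, the initial/final outcomes are labelled secondary in the text and in Table 1, and the main Discussion says the trial is chiefly about load monitoring. What survives is narrower: none of the secondary outcomes is put first for the arm comparison, and the primary outcome cannot serve as one.
- **That any one significant outcome is declared sufficient for efficacy.** The article never says so. The Background hypothesis can be read jointly, and if every outcome had to be significant the false-positive rate could not exceed 5%. The rates above depend on the any-one-of reading. That reading is left open, because no rule is given.
- **That the error rate is a specific figure such as 30%.** That value needs an assumed correlation (0.5 with 11 tests, for instance). Only a range with its assumptions is defensible.
- **That 14 outcomes are tested, or that the Poincaré duplicate is a serious fault.** Pain and Borg are not in the list of compared measures. The duplicate slightly lowers the rate, and nowhere is its agreement with rMSSD offered as corroboration.

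It can also be said that multiplicity for secondary outcomes belongs in an analysis plan not shown here. That is fair for the detail of adjustment. It does not answer the point, because the article itself sets a flat p < 0.05 beside an efficacy hypothesis in three domains and a sample size for one variable.

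Lastly, Trial status reports recruitment complete and data collected, so a lead outcome named now is named late. This is a reason to document the timing. The risk is limited because the statistician is to be blinded and the sample size already fixes the variable.

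**Conclusion.** The point holds in limited form. The trial has an efficacy aim but no designated randomized comparison that decides it, although the sample size shows which one was intended. Under three assumptions (12 outcomes, no true difference on any of them, and any single significant difference taken as support), the false-positive chance is 46% with independence and about 19% at a common correlation of 0.8. That is roughly 4 to 9 times the 5% at which the trial was sized. The correlations are assumptions. The load-monitoring primary outcome is not affected. This is a change that should be made, not a fatal flaw.

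**What to change.** In Secondary outcomes and Statistical analysis, name the between-group comparison of resting rMSSD from the initial/final evaluations as the lead efficacy test at two-sided 5%, in line with the Sample size calculation. Say whether it is made on the final value or on the change, so that it is one test. Label the other initial/final arm comparisons supportive or exploratory and report them as estimates with 95% confidence intervals. If claims in other domains are wanted, test those outcomes after rMSSD in a fixed order or with Holm. Word the Background hypothesis to match, and state that the choice was made before unblinded analysis.

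The change needs no new data or participants and takes no power from the rMSSD test. The small downside is that p < 0.05 on another outcome alone would no longer support an efficacy claim.

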### Randomization

Prior to randomization, baseline data were collected from participants who meet the eligibility criteria and had signed the informed consent form. To maintain the blinding, randomization by group (Pilates group or control group) was performed by another researcher not involved in the recruitment using a computer-generated randomization schedule.

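### The between-group test for the secondary initial/final outcomes is unadjusted for baseline and leaves open what is compared and which test decides; ANCOVA would fix both at almost no cost

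*Protocol article*

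**What the plan says.** The Statistical analysis section sets a Shapiro–Wilk test first. Initial-to-final comparisons of the cardiorespiratory, autonomic and psychometric measures then use a paired t or Wilcoxon test. For the randomized contrast it says: "In the comparison between the groups, the unpaired *t* test or Mann–Whitney test will be used depending on the normality of the data", at p < 0.05. No covariate and no group-by-time term is named. The section also calculates Δ (final minus initial), for the stated purpose of checking differences between the two time points. It does not name Δ as the variable that enters the unpaired test.

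The data for an adjusted analysis exist. The Randomization section states: "Prior to randomization, baseline data were collected from participants who meet the eligibility criteria". The study outline says that the control group has the same initial and final evaluations as the Pilates group.

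The Background words the hypothesis for these measures without reference to the control group: "it is hypothesized that the psychometric, cardiorespiratory, and cardiac autonomic modulation measures will have improved after 12 weeks of training".

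The Sample size calculation section uses rMSSD: "The clinically relevant difference was 19,02 ms and the standard deviation 23,94 ms", at 5% two-sided significance and 80% power. Its result is: "The sample size was calculated to be 25 per group", and then "To account for withdrawals, the sample size was increased by 10% to give 27 volunteers per group".

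**The concern.** Three things are left loose or fixed inefficiently.

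1. **Precision.** Each man has his own baseline value, yet the group comparison is a plain two-sample test. If final values enter it, the baseline is unused. If Δ enters it, the baseline is used, but not in the best way.
2. **What decides.** Two families of tests, within arm and between arms, stand side by side and none is named as decisive. A hypothesis of improvement after training can appear to be answered by a paired test in the Pilates arm alone. Such a test does not use the randomization, and drift common to both arms would pass for benefit.
3. **The normality gate.** A pre-test on small groups decides, outcome by outcome, whether a difference in means or a shift in ranks is tested, so the quantity estimated is not known in advance.

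At stake are the power and clarity of the trial's claim about autonomic and cardiorespiratory effects.

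**Working it through.** **Inputs from the Sample size calculation section.** Difference 19.02 ms, SD 23.94 ms, two-sided 5%, power 80%, 25 per group, 27 with the withdrawal allowance.

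**Assumed.** The baseline–final correlation r is not given; 0.4 to 0.7 is used. The section does not say whether 23.94 ms is the SD of final values or of changes. It is first taken as the SD of final values, with equal SDs at both times.

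**Step 1: the plan's own figure.** n = 2 × [(1.960 + 0.842) × 23.94 / 19.02]² = 24.87, rounded up to 25. The stated figure reproduces as an unadjusted comparison of two means, so no gain from baseline is built in. The normal approximation gives 80.2% power at 25 per group. The noncentral t distribution gives 78.6% at 25 and 81.7% at 27.

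**Step 2: relative variance of the group difference.**
- Final values: 1
- Change scores: 2(1 − r)
- ANCOVA: 1 − r²

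Since 2(1 − r) − (1 − r²) = (1 − r)², which is never negative, ANCOVA is at least as efficient as Δ at every r, apart from one degree of freedom. Δ does worse than final values when r < 0.5 and equals them at r = 0.5.

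**Step 3: power (noncentral t, standardized difference 19.02/23.94 = 0.794, SD multiplied by the square root of the factor above).**

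| r | Variance cut by ANCOVA (r²) | 25 per arm: final / Δ / ANCOVA | 27 per arm: final / Δ / ANCOVA |
|---|---|---|---|
| 0.4 | 16% | 79 / 71 / 85% | 82 / 74 / 88% |
| 0.5 | 25% | 79 / 79 / 89% | 82 / 82 / 91% |
| 0.6 | 36% | 79 / 87 / 93% | 82 / 89 / 95% |
| 0.7 | 49% | 79 / 94 / 97% | 82 / 96 / 98% |

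The row for 25 per arm is the safer guide, because 27 includes the allowance for withdrawals. Charging ANCOVA its extra degree of freedom changes no entry at this rounding.

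**Step 4: the other reading of the SD.** If 23.94 ms is the SD of changes and Δ is compared, the planned power is again 79% at 25 per arm. ANCOVA then multiplies the variance by (1 − r²)/[2(1 − r)] = (1 + r)/2, that is by 0.70 to 0.85. Power becomes 91% at r = 0.4 and 85% at r = 0.7. The gain remains.

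**Step 5: what a within-arm reading would risk.** Suppose both arms shift equally by 5 to 10 ms (assumed), with no training effect. With 25 per arm and an SD of change of 23.94 × √[2(1 − r)], the paired test in the Pilates arm is significant in 17% to 52% of trials at r = 0.5 and in 25% to 74% at r = 0.7. A significant rise in the Pilates arm with none in control occurs in about 14% to 25%. With no shift at all, exactly one arm is significant in 2 × 0.05 × 0.95 = 9.5%.

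**Step 6: the normality gate.** In 10,000 simulated null trials with 25 per group, the two-stage procedure had type I error of 5.3% for normal data and 5.1% for lognormal data. Mann–Whitney was chosen in 10% and 91% of runs. The gate costs almost no type I error; what it changes is the quantity tested.

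**The case against.** The planned unpaired test is a valid comparison of randomized groups, and the sample size was computed for just such a test. Leaving out ANCOVA is a choice, not an error. That stands, and it is why this is an improvement and not a defect that invalidates the analysis.

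A reader might infer more, in two ways:

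- **That training effects will be judged by within-arm paired tests, so that regression to the mean, season or familiarity would be reported as benefit.** The document does not say so. A between-group test at p < 0.05 is planned in the same section, and such drift is expected to affect both randomized arms alike, so that test removes it on average. The hypothesis in the Background is not a decision rule. Misreading within-arm change is permitted by the wording, not prescribed; the figures in Step 5 apply only if the between-group result is set aside.
- **That the group test ignores the baseline.** This is true only if final values are compared. The sentence after the one on the group test introduces Δ without assigning it to the unpaired test or excluding it.

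Two further limits stand. The outcomes concerned are secondary; the primary one is load monitoring during sessions. The size of the gain depends on a correlation that the document does not give. The direction does not: 1 − r² never exceeds 1 or 2(1 − r).

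**Conclusion.** The point holds as a free improvement to the analysis of the secondary initial/final outcomes. The group comparison is valid but unadjusted. The text leaves open whether final values or Δ are compared and which test supports a claim of effect. With 23.94 ms as the SD of final values and r between 0.4 and 0.7, ANCOVA lifts power from 79% to between 85% and 97% at 25 per arm, or from 82% to between 88% and 98% at 27. These figures are for rMSSD in milliseconds; for the other outcomes only the variance factors carry over. The normality gate is a minor part: its cost is an unsettled estimand, not inflated type I error. Nothing here bears on the primary outcome.

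**What to change.** In the Statistical analysis section:

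- Make the between-group analysis of each initial/final outcome an ANCOVA of the final value on group, with that outcome's own baseline value as covariate. Report the adjusted difference with its 95% CI.
- Analyse rMSSD and the low- and high-frequency indices on the log scale at both times. The primary-outcome section already does this for the weekly rMSSD indices.
- Fix the model and scale in advance and drop the Shapiro–Wilk step as a way of choosing the test.
- State that this adjusted difference is the sole basis for any claim of a Pilates effect, and that paired tests and Δ within arms are descriptive.
- Word the hypothesis in the Background as improvement relative to control.

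The cost is a few sentences and one degree of freedom per model. The baselines are already collected, and the SPSS package named in the protocol fits the model. Since data collection is reported as finished, the change should be dated and made while the statistician is still blinded.
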